**Fig. 1 Fig1:**
[figure not shown]
Schematic diagram of participant recruitment and allocation in the STABLE trial

Participants who do not meet the above inclusion criteria will have DAS units removed from their motorcycles, never having entered the trial itself, and the data collected previously will not be used in the STABLE analyses.

### Study intervention

Over the 72 weeks of the study, an estimated 250 students from the 25 clusters, randomised in groups of five clusters, will enter the intervention condition. Each of these participants will receive a free pair of spectacles with spherocylindrical power in each eye as measured during refraction by an optometrist. Refractive power will be based on non-cycloplegic automated refraction (QuickSee, Plenoptika, Cambridge, USA) and subjective refinement. Spectacle-wear compliance will be assessed and recorded throughout the trial based on footage from the driver-facing cameras. Replacement spectacles will be provided free of charge as needed due to loss or breakage. Research staff will communicate with trial participants observed having poor compliance in order to improve their use of the spectacles. Myopia progression in this age group is not expected to be clinically meaningful over the 72 weeks, so there are no provisions for routine re-evaluation of refractive power. However, participants complaining of declining vision or symptoms associated with spectacle wear will be examined at study clinics, with replacement spectacles provided as needed.

### Outcome measures

#### Primary outcome

The primary trial outcome is the number of CNC events per 1000 km driven. Study participants will be asked to meet with research staff every 2 weeks to exchange the USB drives from their DAS units for empty drives. Potential CNC events will be extracted from the DAS recordings using mining algorithms in which kinematic data (lateral and longitudinal acceleration due to hard braking events or the vehicle having fallen on its side) will be passed through filters to discover points at which a CNC event may have occurred. Personnel trained in video reduction will then examine the video footage of the candidate CNC event to assess the content, nature and severity.

An analysis of the probability of CNC events will require the collection and analysis of data from periods (epochs) of motorcycle use free from CNC events. The number of baseline epochs collected for each motorcycle driver will be calculated as a percentage of the total number of kilometres travelled by all drivers during the course of the study. The start-point for each baseline epoch will be randomly selected from the drivers’ video data. If the motorcycle is moving more than 5 km/h, 10 s of video data will be extracted and analysed by video reduction personnel who will record roadway (road type and condition) and traffic variables; riding behaviour (overtaking, speed); riding manoeuvres (turning or going straight, etc.); presence of passengers and environmental conditions (e.g. weather conditions) for each baseline epoch interrogated. Assessors will be masked to the participant’s allocation.

#### Secondary outcomes

Secondary outcomes include self-reported visual function (driving-adapted Visual Function Questionnare-25 [VFQ-25]) [22] administered at baseline and 1 month after receiving spectacles; self-reported crashes and injuries reported every 2 weeks by questionnaire (Crash and Injury Self-Report Questionnaire [CI SRQ]); self-reported crashes (compared with DAS-recorded crashes); and total delivery cost per CNC event avoided in the intervention condition (as an indicator of cost-effectiveness).

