### Study design

STABLE was designed as a SW-CRT because of the ethical concerns inherent in failing to deliver spectacles immediately to persons identified with uncorrected myopia and engaged in a potentially dangerous activity such as driving a motorcycle, as would occur in a traditional trial. The stepped-wedge design involves the sequential transition of clusters from control to intervention conditions in randomised order at 12-week intervals, with spectacles delivered to those needing them as soon as uncorrected myopia is detected. After all participant clusters have undergone vision testing and refraction, all eligible participants will have been exposed to the intervention. This approach balances the ethical requirement to avoid withholding treatment from known myopic drivers and the need to conduct a randomised evaluation of the intervention.

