As shown in Fig. 1, all potential participants enter in the control condition and will have DAS units installed on their motorcycles. However, as they have not yet been examined and refracted, the identity of actual trial participants is not known at that time. Subsequently, during the 14 days before each 12-week period, participants in five randomly selected clusters will undergo an eye examination and refraction. Those meeting the following criteria will receive spectacles within 1 week of the examination and transition to the intervention condition, and their previously collected DAS information will be analysed as control data:Presenting distance visual acuity < 6/12 in the better-seeing eye due to un- or under-corrected myopiaVision correctable with glasses to 6/7.5 or better in both eyesAt least 0.5 D of myopia in both eyes

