### Additional data collection

The following information will be collected by questionnaire from those who fail the WHOeyes self-assessment in at least one eye: age, driving experience, primary means of transport, distance driven per week, motorcycle type, brand, model and engine capacity, and possession of a driving licence. Those meeting the inclusion criteria for DAS fitting and providing informed consent will be asked to provide the following baseline data: exposure to eyecare assessments at time of licensure, visual function (VFQ-25) [22], driver risk profile (Dula Dangerous Driving Index [DDDI]) [24] and economic data including home location (urban or rural), income and estimated monthly expenditures. At the time of the eye examination but before the participant’s cluster transitions to the intervention condition, data will be collected on visual acuity, refractive error, details of current spectacle wear, presence of ocular abnormalities and whether spectacles are required. Data will subsequently be collected on whether spectacles are provided.

Every 2 weeks, participants meeting with study staff to exchange the removable drive in their DAS units will be asked whether they have been involved in a crash in the preceding 2 weeks. Repair and insurance costs will be recorded if a crash occurs. Financial data for the cost-effectiveness calculations from a societal perspective will be captured, including cost of health care received and for crash-related repairs.

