### Statistical analyses

All outcomes for trial participants will be analysed in accordance with the intention-to-treat (ITT) principle. Baseline characteristics will be summarised using means and standard deviations, medians and interquartile ranges, or numbers and percentages, as appropriate. The primary outcome (number of CNC events per 1000 km driven) will be analysed using generalised linear mixed models, reporting mean differences and adjusting for cluster, secular and time effects. For example, secular trend adjustments will take into consideration national and regional driving safety campaigns and calendar time. Seasonal factors (amount of daylight, inclement weather, etc.) are likely to play a role in the number and severity of CNC events. Analysis of secondary outcomes will be done in a similar fashion. Risk differences for binary outcomes and mean differences for continuous outcomes, all adjusting for cluster, secular and time effects, will be reported.

Sensitivity analyses will be conducted to examine the intervention effects, adjusting for additional pre-specified potential confounders including age (years as a continuous variable), DDDI risk profile [24] (total score as a continuous variable) and residence (rural/urban as a binary variable).

Missing data will likely result when participants withdraw from the study or do not complete the full follow-up. Multiple imputations of missing data when assessing secondary outcomes will involve creating 20 copies of the data and imputing missing values by chained equations before averaging the datasets [26].

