### Trial status

This paper is based on version 4.2 of the STABLE protocol (dated 15 May 2024). Important changes to the protocol will be communicated to the relevant ethics committees and trial registries as needed. Recruitment to STABLE is expected to start and be completed (given the stepped-wedge design which requires all participants to be included at the outset) in the fourth quarter of 2024.

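### Every control VFQ-25 value is taken at entry and every later one after spectacles, so the promised time-adjusted effect has no concurrent controls

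*Protocol article*

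**What the plan says.** The Secondary outcomes section has the VFQ-25 "administered at baseline and 1 month after receiving spectacles", which is two measurements per participant.

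Additional data collection fixes when baseline is. It is the point of consent and DAS fitting, because those students are "asked to provide the following baseline data: exposure to eyecare assessments at time of licensure, visual function (VFQ-25" and other items. The same section lists separately what is recorded at the pre-switch eye examination: "data will be collected on visual acuity, refractive error, details of current spectacle wear, presence of ocular abnormalities and whether spectacles are required". The VFQ-25 is not in that list.

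At entry, "all potential participants enter in the control condition and will have DAS units installed on their motorcycles" (Participants and recruitment procedure). Trial status describes recruitment as a single phase, "given the stepped-wedge design which requires all participants to be included at the outset". Study design then has the "sequential transition of clusters from control to intervention conditions in randomised order at 12-week intervals".

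Statistical analyses treats secondary outcomes like the primary one: "Risk differences for binary outcomes and mean differences for continuous outcomes, all adjusting for cluster, secular and time effects, will be reported".

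**The concern.** A stepped-wedge trial separates the intervention from calendar time by comparing clusters that have crossed over with clusters that have not, within the same period. That requires the outcome to be measured in both kinds of cluster at about the same time. The VFQ-25 schedule never does this. All control values come from the entry window, and all values after the first step come from participants already wearing trial spectacles.

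At stake is the meaning of the VFQ-25 result. Season, riding experience and answering the questionnaire a second time could all move a self-reported score, and the schedule offers no way to separate such movement from the effect of spectacles. The randomised order of crossing over contributes no concurrent comparison for this outcome.

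**Working it through.** The article gives no sample size, power or effect for the VFQ-25, so there is no stated figure to reproduce. The check is whether the planned effect can be estimated.

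**Inputs**
- 25 clusters crossing over in groups of five at 12-week intervals, over 72 weeks (Study intervention; Study design).
- One VFQ-25 at entry (period 0, control). One VFQ-25 about 4 weeks after the step for the clusters of sequence s (period s, intervention), for s = 1 to 5.
- Assumed timing: entry at week 0 and step s at week 12s, so the second measure falls at week 12s + 4.

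**Spacing.** Sequence 1: 12×1 + 4 = 16 weeks. Sequence 5: 12×5 + 4 = 64 weeks. Mean: 12×3 + 4 = 40 weeks.

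**Categorical time.** The columns are intercept, treatment and five indicators for periods 1 to 5, seven in all. Treatment is 0 in period 0 and 1 in every later row, so

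treatment = P1 + P2 + P3 + P4 + P5.

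The rank is 6 of 7. With cluster fixed effects (24 more columns) it is 30 of 31, and it is 30 whether or not treatment is included. The identity does not depend on the number of steps, so it would hold equally for the six sequences named in the Sample size section.

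**Smooth time.** Illustrative standard errors, in SD units, come from generalised least squares on cluster means: SE = square root of the treatment element of (X′V⁻¹X)⁻¹. I used 7 participants per cluster and ICC 0.02, both given for the crash outcome and assumed here for the VFQ-25. Individual autocorrelation is 0, with random cluster effects. The unadjusted value follows by hand: √[2 × (1 − 0.02)/7 ÷ 25] = √0.0112 = 0.106.

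| Time adjustment | SE (SD units) |
|---|---|
| none | 0.106 |
| linear | 0.215 |
| linear plus annual season | 0.384 |
| quadratic | 0.483 |
| cubic | 1.295 |
| categorical period | not estimable |

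A linear trend doubles the SE (0.215/0.106 ≈ 2) and a cubic multiplies it by about 12 (1.295/0.106). Each smooth-trend estimate depends on carrying the curve fitted across the five post-spectacle times back to week 0, where there are no treated data to check it.

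**No time adjustment.** Any drift goes straight into the effect. If the score drifted by an assumed 0.05 to 0.10 SD per 12 weeks, the average bias would be 0.05 × 40/12 = 0.17 SD to 0.10 × 40/12 = 0.33 SD. The documents give no drift figure; these values only show scale.

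**With control values added.** Giving the VFQ-25 to clusters not yet crossed over, 4 weeks after each of steps 1 to 4, yields rank 7 of 7 (31 of 31 with cluster effects) and, from the same formula, SE 0.107 with categorical periods. One VFQ-25 at the pre-switch examination of sequences 2 to 5 also yields rank 7 of 7 and SE 0.120. The examination of sequence s + 1 falls at about week 12(s + 1) − 2 = 12s + 10. That is in the same 12-week period as the post-spectacle measure of sequence s at week 12s + 4.

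**The case against.** **The form of time is not stated.** The article speaks of calendar time, campaigns and season but never says that period is categorical, and the analysis plan may settle this. A reader might infer that the effect cannot be estimated at all, or that the analysis must either fail or drop time. The documents do not support that: the staggered second measures allow a smooth trend to be fitted. What remains is that such an estimate relies on extrapolation. No analysis plan or multiple imputation can supply concurrent control values that were never collected.

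**The timing is assumed.** A reader might take it that everyone completes the first VFQ-25 at the same moment. The article gives only a recruitment window, the fourth quarter of 2024. Examinations fall in the 14 days before each period, with spectacles within a week, so the second measure can shift by a week or two. The 16 and 64 weeks are therefore approximate. Spread in entry dates creates no control values after the first step, so the aliasing stands.

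**Drift may be small.** The article does not expect clinically meaningful myopia progression over 72 weeks. That bears on the size of any bias from this one source. It does not make a self-reported driving score stable against season, experience or repeat administration, and the article itself commits to adjusting for time.

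**Conclusion.** The point holds for the VFQ-25. With categorical period effects the promised adjusted mean difference is not estimable (rank 6 of 7; 30 with or without treatment once cluster effects are added). With a smooth trend it is estimable, but only through an untestable shape extrapolated to entry, at an SE about 2 (linear) to 12 (cubic) times the unadjusted one under the borrowed ICC and zero autocorrelation. Without time adjustment it is an uncontrolled before-after contrast over roughly 16 to 64 weeks.

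The aliasing rests on reading baseline as entry, which Additional data collection supports, and on all entry values preceding the first step, which Trial status supports.

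A reader might extend this to the whole trial. That would be wrong: the primary outcome from continuous DAS recording and the two-weekly self-reported crashes have both conditions in the same periods. This is a weakness in one named secondary outcome. It should be corrected before the first step, because control values missed then cannot be recovered.

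**What to change.** Collect control VFQ-25 values after the first step, at visits already planned.

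- **Option (a):** at the two-weekly USB exchange about 4 weeks after each of the first four steps, also give the VFQ-25 to clusters that have not yet crossed over. Controls are then directly concurrent. Cost: at most 25 × (20 + 15 + 10 + 5) = 1,250 forms. On the article's 40% estimate, about 0.40 × 1,250 = 500 come from participants later found eligible. All must be asked because eligibility is unknown until the examination.
- **Option (b), leaner:** give one VFQ-25 at the pre-switch eye examination, before spectacles. Cost: at most 25 × 25 = 625 forms, about 250 of them from eligible participants. Controls are concurrent only within 12-week periods, since the two measures lie about 6 weeks apart.

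Either gives rank 7 of 7. The downsides are modest participant burden, unused forms from students later excluded, and possible repeat-administration effects, which are greater under (a): sequence 5 would complete the form six times (entry, four control rounds, one after spectacles). No extra visit is needed; the article does not say who administers the form, so staff time should be confirmed.

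If neither option is adopted, amend Statistical analyses so that the VFQ-25 is reported as an uncontrolled before-after change, and not as a time-adjusted randomised effect.

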### Sample size

Unpublished data from Dynamic Vision, an organisation currently collecting CNC events from motorcycle drivers in Vietnam, were used to inform the power calculation. Results showed an estimated mean event rate of 1.67 CNC events per 1000 km driven (standard deviation [SD] = 0.556). For a postulated, clinically meaningful 10% reduction in CNC events, a stepped-wedge cohort design comprising six sequences of seven myopic participants per cluster (a 28% prevalence, below the 40% figure observed during pilot testing with the WHOeyes app), a coefficient of variation of cluster sizes of 3, and five clusters per sequence with Individual Auto Correlation (IAC) of zero, confer 90% power (mean difference = 0.167, SD = 0.556; intraclass correlation [ICC] = 0.02 [0.01–0.05]) [23]. This would be achieved by collecting DAS data from 175 students over the course of 72 weeks. To achieve this, 5200 students will be invited to self-assess their vision using WHOeyes. Pilot data indicate that approximately 12%, or 625 students, will fail that assessment and be eligible to join the preliminary phase of the study, with placement of DAS units on their motorcycles. An estimated 250 (40% of those failing the WHOeyes self-assessment) will have eligible, uncorrected/under-corrected myopia detected on their subsequent eye examination by an optometrist. They will then be assigned to the intervention condition and given free spectacles. With a 30% dropout rate, this will result in complete datasets for 175 participants over the course of the trial.

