**Methods:**

This investigator-masked, stepped-wedge, cluster randomised naturalistic driving trial will recruit 625 students aged 18–23 years, driving ≥ 50 km/week, with ≥ 1-year driving experience and using motorcycles as their primary means of transport, in 25 clusters of 25 students in Ho Chi Minh City, Vietnam. Motorcycles of consenting students who have failed self-testing on the WHOeyes app will be fitted with Data Acquisition Systems (DAS) with video cameras and accelerometers. Video clips (± 30 s) of events flagged by the accelerometer will be reviewed for crash and near-crash events per 1000 km driven (main outcome). Five clusters of 25 students will be randomly selected every 12 weeks to undergo ocular examination and an estimated 40% of these will have bilateral spherical equivalent < − 0.5 D, and better-eye presenting distance visual acuity < 6/12, correctable bilaterally to ≥ 6/7.5. They will be given free distance spectacles and their driving data before receiving spectacles will be analysed as the control condition and subsequent data as the intervention condition. Secondary outcomes include visual function, cost-effectiveness and self-reported crash events.

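### The SD of 0.556 behind the 90% power claim is too small for an event count unless riders average about 375–450 km/week, and no mean mileage is stated

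*Protocol article*

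**What the plan says.** All the power inputs are in the Sample size section of the protocol article. The rate and its spread come from unpublished data: "Results showed an estimated mean event rate of 1.67 CNC events per 1000 km driven (standard deviation [SD] = 0.556". The target is given as "For a postulated, clinically meaningful 10% reduction in CNC events", which is 0.167 events per 1000 km. The design is described as "a stepped-wedge cohort design comprising six sequences of seven myopic participants per cluster", with "five clusters per sequence with Individual Auto Correlation (IAC) of zero", and the result is stated as "confer 90% power (mean difference = 0.167, SD = 0.556; intraclass correlation [ICC] = 0.02 [0.01–0.05". The section also gives a coefficient of variation of cluster sizes of 3, and 175 complete datasets over 72 weeks.

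The abstract's Methods paragraph describes the trial "in 25 clusters of 25 students in Ho Chi Minh City, Vietnam", and the Study design section describes "sequential transition of clusters from control to intervention conditions in randomised order at 12-week intervals". Seventy-two weeks in 12-week steps is six periods. Twenty-five clusters taken five at a time is five sequences.

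The article does not say what distance or driving time the SD of 0.556 refers to. It gives no expected mean mileage, total distance or total number of events. The only mileages are self-reported entry minimums: 50 km/week in the abstract and 25 km/week in the inclusion list under Participants and recruitment procedure.

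**The concern.** The primary outcome is a number of events divided by distance driven. Even if every rider had the same underlying risk, a rate observed over a short distance would vary because events are few. For independent counts this sets a minimum variance that depends only on the event rate and the distance. At the entry mileages a participant has about 0.5 to 1 expected event per 12-week period, so the observed rate per 1000 km must vary widely from period to period. An SD of 0.556 on a mean of 1.67 leaves no room for that.

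The 90% is the article's stated justification for the trial's size. If the true power for a 10% reduction is much lower, a null result read against a 90% claim would be taken as evidence that spectacles do not help, when the trial may have had little chance of detecting the effect it names. The article plans no interim analysis of outcomes and intends its findings to reach policy makers.

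**Working it through.** **Inputs.** From the Sample size section: rate 1.67 per 1000 km, SD 0.556, difference 0.167, ICC 0.02, individual autocorrelation zero, 7 participants per cluster, 175 participants, 72 weeks. From the abstract and Study design: 25 clusters and 12-week steps. Assumed: two-sided 5% test, because the article states no alpha.

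**Step 1: reproduce the stated power.** The stepped-wedge (Hussey–Hughes) variance on cluster-period means, with fixed period effects and a random cluster effect, is

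Var = I·s·(s + T·t) / [(I·U − W)·s + (U² + I·T·U − T·W − I·V)·t]

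where s is the residual variance divided by 7 and t is the between-cluster variance. With I = 25 clusters, T = 6 periods and five sequences of five clusters, U = 75, W = 1,375 and V = 275. The two brackets are then 500 and 1,750.

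- s = 0.98 × 0.556² / 7 = 0.0433; t = 0.02 × 0.556² = 0.00618
- Var = 0.00268, SE = 0.0518
- 0.167 / 0.0518 = 3.23; power = Φ(3.23 − 1.96) = 89.7%

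This matches the stated 90%. It does so with 0.556 as the SD of one participant's rate in one 12-week period. Two stated inputs are not used in the match. Taking six sequences literally (30 clusters, seven periods) gives 97.0%, which does not match. The cluster-size coefficient of variation of 3 is not applied.

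**Step 2: the minimum SD for a rate.** For independent counts, the variance of a rate per 1000 km is at least 1.67 / (thousand km).

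- 25 km/week: 300 km per period, 0.5 expected events, SD = √(1.67/0.3) = 2.36
- 50 km/week: 600 km, 1.0 expected event, SD = √(1.67/0.6) = 1.67
- Distance at which the minimum SD equals 0.556: 1.67/0.556² = 5.40 thousand km per 12 weeks, or 5,400/12 = 450 km/week

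**Step 3: power with the minimum SD in the same formula.** The lower figure keeps 2% of this variance between clusters. The higher figure assumes no cluster variance, when Var reduces to s/20.

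| Mean km/week | Minimum SD | Power, ICC 0.02 kept | Power, no cluster variance |
|---|---|---|---|
| 25 | 2.36 | 12% | 13% |
| 50 | 1.67 | 19% | 22% |
| 100 | 1.18 | 33% | 39% |
| 200 | 0.83 | 58% | 66% |
| 300 | 0.68 | 75% | 83% |
| 375 | 0.61 | 84% | 90% |
| 450 | 0.56 | 90% | 94% |

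At 50 km/week the SE is 0.155 (ICC kept) or 0.141 (no cluster variance). The reduction detectable with 90% power is 3.24 × SE / 1.67, or 30% and 27% respectively.

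**Step 4: a check that does not depend on what 0.556 means.** Ignore clustering and period effects, and split all driving equally between the two conditions. At 50 km/week, 175 × 72 × 50 = 630,000 km gives 526 control and 473 intervention events. SE(log rate ratio) = √(1/526 + 1/473) = 0.0634; |ln 0.9| / 0.0634 = 1.66; power 38%. At 25 km/week it is 22%. Even this idealised comparison needs about 3,800 events, roughly 190 km/week, for 90%.

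**The case against.** **The mileages are minimums.** Participants must use the motorcycle as their main transport, so the mean will exceed the entry threshold. This stands. A reader might infer from the first rows of the table that the trial's power is 12–22%. The documents do not support that: those figures describe riders who all sit exactly at a threshold for 72 weeks. What survives is the dependence on mileage. At 200 km/week, four to eight times the minimums, power is still at most 66%.

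**The meaning of 0.556 is inferred.** The article does not say it is a per-period SD, and the match in Step 1 sets aside two stated inputs. This also stands as a limit on what can be said about how the figure was obtained. It does not rescue the figure. If 0.556 is a between-rider SD of long-run rates, or an SD over the whole study (5,400 km over 72 weeks is 75 km/week), it is the wrong input for this formula because the period-level counting variation has been left out. Step 4 does not use the SD at all.

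**The full protocol or the data source may document the mileage.** It may, and an article need not carry every detail, so the missing mileage is not itself the fault. The point is that the rate, SD and power printed together are compatible only at a mileage far above any the article mentions.

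**More than 175 may contribute.** With intention-to-treat analysis, some of the 250 eligible participants will give partial data. At the upper limit of all 250 retained (10 per cluster) and no cluster variance, power is 29% at 50 km/week and 52% at 100, and 90% needs about 375 × 7/10 = 262 km/week. The gap narrows but does not close.

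**Poisson is an assumption.** It is the favourable one for independent counts, since overdispersion raises the variance. A positive individual autocorrelation could recover stable differences between riders but not the counting variation, which is not shared between periods.

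**Conclusion.** The concern holds in conditional form. The stated 90% power for a 10% reduction relies on an SD that a count outcome at 1.67 events per 1000 km can have only at about 450 km/week. With the counting variance included, 90% is reached at about 375 km/week with no cluster variance and 450 km/week with ICC 0.02 kept. These are roughly 7 to 18 times the entry minimums (375/50 = 7.5; 450/25 = 18). At intermediate mean mileages of 100 to 300 km/week, power is between 33% and 83%.

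This rests on a two-sided 5% test, independent counts at the stated control rate, 7 participants per cluster with complete data, equal cluster sizes and five sequences. It does not establish the trial's actual power, because mean mileage is not stated. A flat statement that the design lacks 90% power would go further than the documents allow. What they do show is that the claim is unsupported as written and implausible at modest mileages.

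**What to change.** Replace the calculation in the Sample size section with one for a rate outcome that includes counting variance. State:

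- the distance per driver, or observation period, to which the SD of 0.556 refers
- the expected mean distance per participant per 12 weeks, with its source
- the expected total number of events in each condition
- the between-driver variance and ICC
- the actual number of sequences, and the cluster-size variation used

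Then restate the power for a 10% reduction and the reductions detectable with 80% and 90% power. Keep the 90% claim only if the documented mean mileage supports it, roughly 375–450 km/week under the current design with 175 complete participants. A log-rate model with distance as offset is the natural basis, but any method consistent with the planned mixed-model analysis will do if it carries the counting variance.

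The cost is a recalculation and amended wording. No extra enrolment or change to trial conduct is needed. The downside is a stated power that will probably be less favourable.
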